### Data analysis

The main comparisons will be the self-reported 7 days PP quit rate among groups, which include: (1) Active referral plus brief advice vs. control: to test the bulk model of active referral with referral card plus brief counselling using AWARD model with smoking harms and cessation leaflet intervention effects; (2) Brief advice vs. control: to test brief counselling using AWARD model with smoking harms and cessation leaflet intervention effects; and (3) Active referral vs. brief advice: to test active referral with referral card intervention effects.

The intention-to-treat (ITT) principle will be used for outcome comparison between groups. Information missed at follow-up will be considered as non-quitters, non-reducers or do not use SC service if no records from the service providers are available for verification. Methods to handle missing cases (multiple imputations or complete case analysis) will depend on the proportion of actual percentages of the attrition rate. Baseline characteristics and outcome measures among groups at each endpoint will be compared using chi-square tests, Mann–Whitney tests and *t*-tests. Logistic regression will be used to predict quitting and models will be adjusted for baseline differences if necessary. Multi-level analysis method will be used to handle clustering effects.

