### Sample-size calculation

The sample size calculation is based on the primary outcome of self-reported 7-day PP quit rate at the 3-month follow-up. Based on the previous similar studies conducted in the community in Hong Kong, the 3-month quit rate for the control group was approximately 10.0 % [19, 22, 23]. According to the RCT of active referral conducted by Borland et al. [10], the rate ratio of quit rate for the intervention and control group was 1.92 (intervention group: 12.3 %, control group: 6.9 %). Therefore, the effect size for the intervention in this study is set conservatively at 1.60. The quit rate for the intervention group (a combination of active referral and brief advice groups) versus the control group is 16.0 and 10.0 % respectively. To detect a significant difference of quit rate between intervention and control groups with a power of 80 and 5 % significance level, we will need 284 subjects per group. Assuming an intra-cluster correlation coefficient as 0.005 and retention rate of 70 % at the 3-month follow-up, the total sample size taking into account in the intra-cluster correlation within each recruitment session and attrition is 1291.

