#### Active referral

Subjects will receive a referral card and be actively referred to one of the five major SC services in Hong Kong, including (1) Department of Health SC Services, (2) Tung Wah Group Hospital Integrated Center on SC, (3) Hospital Authority (HA) SC Clinics, (4) Pok Oi Hospital Chinese Medicine SC Services, and (5) University of Hong Kong Youth Quit-line. The details of each service are shown in Table 2. The well-trained SC ambassadors will explain the SC services to the subjects who will be asked to choose one of the SC services to be referred. Informed written consent and contact telephone number of the subjects will be obtained at the recruitment site, processed primarily in the university research office (including putting subjects’ information into computer), transferred to the collaborator - COSH (Hong Kong Council on Smoking and Health) and eventually destined at the selected service provider within 7 days. As proactive phone call service is not available in HA Clinics, subjects will be encouraged to make the appointment by themselves using a provided list of HA clinics contact addresses and telephone numbers. Research staff will monitor SC services use of the subjects and assist them to make or re-make the appointment if necessary in each follow-up (1-, 2-, 3- and 6- month).

**Table 2 Tab2:** Major smoking cessation services in Hong Kong

	Main services
Department of Health	Phone SC counselling managed by registered nurses.
Hospital Authority	SC clinics run by physicians and nurses.
	Free nicotine replacement therapy (NRT) and cessation drugs.
Tung Wah Group of Hospitals	SC clinics run by physician, nurses, and social worker.
	Free nicotine replacement therapy (NRT) and cessation drugs.
Pok Oi Hospital	SC clinics run by Chinese medical practitioners.
	Free acupuncture cessation therapy.
Youth Quit-line	Telephone counselling by well-trained youth smoking cessation counsellors.

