#### Follow-up

Follow-up telephone calls will be conducted at 1-, 2-, 3- and 6-months after the baseline to assess changes in smoking habits and progress of quitting especially the use of referred SC services. Subjects who reported not smoking in past 7 days at the 3- and 6-month follow-up will be furthered assessed by inviting their relatives/friends for verification (non-biochemical validation) and will be biochemically validated using the exhaled carbon monoxide and saliva cotinine tests.

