#### Secondary outcomes

Secondary outcomes at 3- and 6-month follow-up include:SC service use and indicators of use: calling a hotline, making an SC appointment, SC clinic attendance and counselling session attendance. Information of self-reported SC service use of active referral group will be verified with service providers’ records.Biochemical validated smoking abstinence: Smoking abstinence will be defined as exhaled carbon monoxide (CO) level <4 ppm and saliva cotinine level <10 ng/ml [25, 26].Smoking reduction: cigarette consumption reduced by at least 50 % compared with the baseline.

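### The missing-equals-non-user rule names only provider records as an exception, so a participant who reported service use earlier and misses the 3- or 6-month call can be analysed as a non-user

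*Protocol article*

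**What the plan says.** Four parts of the protocol article bear on this point.

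- **Follow-up:** "Follow-up telephone calls will be conducted at 1-, 2-, 3- and 6-months after the baseline". Their purpose includes assessing "progress of quitting especially the use of referred SC services". The Active referral section adds: "Research staff will monitor SC services use of the subjects and assist them to make or re-make the appointment if necessary in each follow-up", and lists the same four time points.
- **Secondary outcomes:** the list opens with "Secondary outcomes at 3- and 6-month follow-up include". Its first item is "SC service use and indicators of use: calling a hotline, making an SC appointment, SC clinic attendance and counselling session attendance". No look-back window is given. The same item plans a check of self-reported use against provider records for the active referral group only.
- **Data analysis:** "Information missed at follow-up will be considered as non-quitters, non-reducers or do not use SC service if no records from the service providers are available". The next sentence leaves other methods open: "Methods to handle missing cases (multiple imputations or complete case analysis) will depend on the proportion of actual percentages of the attrition rate".
- **Sample-size calculation:** the only attrition figure is a "retention rate of 70 % at the 3-month follow-up". No 6-month figure is given, and no rate of service use appears as a planning assumption.

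**The concern.** One rule covers two kinds of outcome. Counting a missing participant as a smoker is a usual convention for 7-day point prevalence, because current smoking status can reverse between calls. Having phoned a hotline or attended a clinic cannot reverse. If someone reported a visit at month 1, silence at month 3 does not remove it.

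The rule names one thing that protects a lost participant from being coded a non-user, namely a provider record. A positive self-report already in the trial database is not named. Two analysts following the text could therefore code the same person differently.

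The between-arm comparison of service use is at stake, and this is the outcome closest to what active referral is meant to change. Discarded reports lower measured use, by an amount that depends on loss, on how many of the lost had already reported use, and on how many have a record. All three can differ by arm. Record access is planned to differ.

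**Working it through.** **Step 1. One participant under each reading.** Take a participant who reports a clinic visit at month 1, cannot be reached at month 3 and has no provider record.

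| Reading of the Data analysis section | 3-month service use |
|---|---|
| Rule applied to the missed 3-month call, provider record the only exception | Non-user |
| Only the missing report is affected, earlier report kept | User |
| Complete case analysis | Excluded |
| Multiple imputation | Imputed; whether the earlier report is used is not stated |

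The text does not choose among these. The first row is the literal one.

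**Step 2. Number lost.** The stated total of 1291 is the number recruited before loss, and it can be reproduced. Three groups of 284 give 852. Over 66 sessions that is 852/66 = 12.9, about 13 per session. The design effect is 1 + (13 − 1) × 0.005 = 1.06, and 852 × 1.06/0.70 = 1290.2, which rounds up to 1291. Loss at 3 months is therefore 0.30 × 1291 = 387 participants, or 129 per arm if the arms are equal in size.

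**Step 3. Fall in measured use.** Let e be the share of the lost who reported use at an earlier call, have no provider record and are recoded. The fall, as a share of all randomised, is 0.30 × e. The article gives no value for e, so a range is shown.

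| e | Fall in measured use (points) | Participants per arm (129.1 × e) |
|---|---|---|
| 0 (earlier reports kept) | 0 | 0 |
| 5 % | 1.5 | 6.5 |
| 10 % | 3.0 | 12.9 |
| 15 % | 4.5 | 19.4 |

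The same calculation cannot be done for 6 months, because no 6-month retention is stated.

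**Step 4. Difference between arms.** Let s be the share of the lost who had reported use earlier, and r the fraction of these with a provider record. If earlier reports are not counted, the fall is 0.30 × s × (1 − r).

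- Equal s of 10 %, with r = 1 in active referral and r = 0 elsewhere: the falls are 0 and 3.0 points, a spurious 3.0 points in favour of active referral.
- s of 15 % in active referral and 5 % in control, with r = 0 in both: the falls are 4.5 and 1.5 points, so the true difference is understated by 3.0 points.

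Both cases are illustrations. They show that the direction is not fixed in advance.

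**The case against.** The strongest reply is that the article nowhere says an earlier report is overwritten. The rule concerns information that was missed, and a visit reported at month 1 was not missed. If use is cumulative, that report already settles status at month 3. If use is counted per interval, a lower figure at 6 months than at 3 is legitimate. This stands as far as it goes. A reader might infer that the trial erases positive reports in every arm and records those people as never having used a service, but that goes beyond the text. The article never calls service use cumulative, and it does not establish that the 1- and 2-month answers feed no outcome.

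The safeguards also count. The provider-record exception is not itself limited to one arm, and multiple imputation or complete case analysis remains possible. Neither closes the gap. The only planned use of records concerns active referral. Complete case analysis would drop the reported user, and neither method is said to draw on earlier calls.

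A larger size is tempting. If 50 to 80 % of those lost at month 3 had answered a 1- or 2-month call, and lost and retained participants used services equally, then 0.30 × 0.50 = 15 % to 0.30 × 0.80 = 24 % of users by month 2 would be recoded. The contact shares are invented. The sum also ignores record rescue, treats one early call as capturing all use to month 2, and excludes zero. The document does not support it as an estimate.

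Last, deriving an endpoint from several calls is often left to an analysis plan. That would answer a mere omission. Here the article fixes a rule and names its exception, and the exception leaves out information the trial already collects.

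**Conclusion.** The point holds as a badly specified rule. Read as written, it allows a reported user to be analysed as a non-user, and the one rescue it names may work mainly in the active referral arm. It does not show that such recoding will happen.

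The fall in measured use at 3 months is 0 points if earlier reports are kept, and 1.5 to 4.5 points if 5 to 15 % of those lost are recoded. Of these inputs, only the 30 % loss comes from the protocol. Any bias between arms also needs the arms to differ in loss, earlier reporting or record access; only a difference in planned record access is documented.

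Service use is a secondary outcome. The primary point-prevalence quit rate is unchanged, because the argument about irreversible events does not apply to it.

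**What to change.** In the Secondary outcomes and Data analysis sections:

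1. Define service use at 3 months, and likewise at 6 months, as any use since baseline reported at any call up to that time point.
2. Apply missing equals non-user only to participants with no report of use at any call up to that time point.
3. Use the same self-report source in all arms for the between-arm comparison, and state that the question on use is asked in the same form in each arm. Keep provider records for verification or a sensitivity analysis.

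This costs a few sentences. The calls are already scheduled, so it adds no contact, and the sample size and primary analysis are untouched.

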**Methods/Design:**

This is a single-blinded, parallel three-armed cluster randomized controlled trial (RCT) with two treatment groups of (1) brief SC advice using the AWARD model, active referral to SC services plus a referral card and a health warning leaflet (active referral group) and (2) brief SC advice using AWARD model and health warning leaflet (brief advice group) and a control group receives general very brief advice with a self-help booklet. A total of 1291 smokers will be recruited from 66 clusters (recruitment sessions) with 22 will be allocated to each of the two intervention and one control groups. SC ambassadors will be trained for delivering the interventions and conducting telephone follow-up. The primary outcomes are self-reported 7-days point prevalence (PP) abstinence at 3 and 6 months follow-up. Intention-to-treat principle and multi-level regressions will be used for data analysis.

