## Methods/Design

### Overview of design

This is a single-blinded, parallel three-armed cluster RCT with 1291 smokers aged 18 or above will be recruited from the community (Fig. 1). Cluster randomization will be used based on the recruitment sessions (total 66 sessions) to assign participants to one of three conditions of (1) brief SC advice using AWARD model, active referral to current SC services plus a referral card and a health warning leaflet (active referral group); (2) brief SC advice using AWARD model and health warning leaflet (brief advice group); or (3) self-help booklet with general advices (control group). The trial will follow the CONSORT criteria [20].

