### Data collection

#### Baseline

Demographics including gender, age, marital status, number of children, type of residence, educational level, employment status and household income will be collected. Average number of cigarettes smoked per day, the age starting smoking and the usual time having the first cigarette smoked each day, attempts to quit or reduce, methods used in past quitting attempts, reasons of not currently using the SC services, readiness (decisional date to quit) and perceived importance, difficulties and confidence to quit smoking, and knowledge about smoking (e-cigarette and risk of smoking) will be collected using validated questions.

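### The analysis section names tests that ignore the randomised sessions beside a multi-level method without saying which governs inference, and it lets observed baseline differences choose the covariates

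*Protocol article*

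**What the plan says.** The abstract gives the design: participants are "recruited from 66 clusters (recruitment sessions) with 22 will be allocated to each of the two intervention and one control groups". The Cluster randomization section has everyone recruited at one activity receive the same allocation, so the session is the unit of randomisation. The Sample-size calculation section allows for this: "Assuming an intra-cluster correlation coefficient as 0.005", with a "retention rate of 70 % at the 3-month follow-up".

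The Data analysis section then makes three statements about the outcome analysis:
- "outcome measures among groups at each endpoint will be compared using chi-square tests", with Mann-Whitney and t-tests in the same sentence, which also covers baseline characteristics.
- Logistic regression will be used for quitting, and "models will be adjusted for baseline differences if necessary".
- A multi-level method will deal with clustering.

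The abstract, in its single sentence on analysis, names intention-to-treat and multi-level regressions, and no simple tests. Neither place says whether the simple tests, the logistic model or the multi-level model yields the primary result. The Baseline section shows that cigarettes per day, time of first cigarette, past attempts to quit or reduce, "readiness (decisional date to quit) and perceived importance, difficulties and confidence to quit smoking", age and gender are all recorded.

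**The concern.** Two stated rules are at issue.

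The first is the choice of test. Chi-square, Mann-Whitney and t-tests all assume independent participants. With sessions randomised, and outcomes positively correlated within a session as the sample size assumes, such tests understate the standard error and reject a true null hypothesis more often than 5 % of the time. Because the multi-level method stands beside these tests and is not stated to replace them, one outcome can yield two p-values with no stated order. The Data analysis section lists three main comparisons and the Primary outcome section gives two time points, so there are 3 x 2 = 6 primary contrasts. If each can be reported from a simple test, an unadjusted multi-level model and a baseline-adjusted model, there are up to 6 x 3 = 18 candidate primary results.

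The second is the choice of covariates. Adjusting when baseline looks different lets chance imbalance decide which model is fitted, so the primary estimate is not fixed before the data are seen. The criterion is not stated. If it were the baseline tests in the same section, those also ignore sessions and would flag differences too often wherever baseline characteristics cluster by session.

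**Working it through.** **Inputs from the protocol article**
- Total recruited: 1291 (abstract).
- Sessions: 66, with 22 per arm (abstract).
- Intra-cluster correlation (ICC): 0.005; retention: 70 %; 284 per group before inflation (Sample-size calculation).
- Missing outcomes count as non-quitters, but multiple imputation or complete-case analysis may be chosen according to attrition (Data analysis). The number analysed per session therefore lies between the retained and the recruited count.

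**Reproducing the plan's clustering allowance.** Take 284 per group as given; how that figure was reached is a separate matter. Three groups give 3 x 284 = 852, or 852/66 = 12.9, about 13 per session. The design effect is DE = 1 + (m - 1) x ICC = 1 + 12 x 0.005 = 1.06. Then 852 x 1.06 / 0.70 = 1290.2, which rounds up to the stated 1291. The plan's sample size thus rests on an analysis that accounts for sessions.

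**Effect of a test that ignores sessions.** Three formulas apply:
- DE = 1 + (m - 1) x ICC
- shortfall in the standard error = 1 - 1/sqrt(DE)
- true two-sided error = 2 x [1 - Phi(1.96/sqrt(DE))]

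| Analysed per session | m | DE at ICC 0.005 | Standard error too small by | True error of a 5 % test |
|---|---|---|---|---|
| Retained only | 1291 x 0.70/66 = 13.7 | 1.063 | 3.0 % | 5.7 % |
| All recruited | 1291/66 = 19.6 | 1.093 | 4.3 % | 6.1 % |

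A beta-binomial simulation (22 against 22 sessions, 10 % quit rate in both arms, 200,000 runs) gave 5.9 % with 14 per session and 6.1 % with 20, in line with the formula.

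**Sensitivity to session size.** The table assumes equal sessions. With unequal sessions, DE = 1 + [(1 + CV^2) x m - 1] x ICC, where CV is the coefficient of variation of session size. The article gives no CV. For assumed values of 0.4 and 0.8 at m = 19.6, DE is 1.108 and 1.155, and the true error about 6.3 % and 6.8 %.

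**Covariate rule.** No arithmetic applies. The text makes adjustment conditional on what baseline shows; every variable a fixed set would need is already in the Baseline section.

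**The case against.** The strongest reply is that clustering is already handled. The Data analysis paragraph ends with a multi-level method, the abstract names multi-level regressions as the analysis, and the sample size is inflated for the ICC. The paragraph can be read naturally as a sequence: crude comparison, then logistic regression, then a multi-level version to account for sessions. This stands to a large extent. A reader who saw only the sentence on chi-square tests might infer that the trial's standard errors will be too small; the documents do not support that as an unconditional statement. It holds only if the simple tests carry the inference, and no passage says that they do. What remains is that no passage says that they do not.

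It can also be said that the outcomes are essentially binary, so the Mann-Whitney and t-tests will mostly serve baseline variables. That is fair: for the quit rates the test at issue is chi-square.

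A third reply is that a covariate list and an order of analyses are commonly left to the full analysis plan. Their absence from a journal article is indeed no finding. The conditional adjustment rule is different, because it is stated text and it fixes the matter badly.

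Two stronger readings are tempting. One is that the error could be far higher: the same formula gives 8.0-9.4 % at an assumed ICC of 0.02 and 12.5-15.8 % at 0.05. These are 4 and 10 times the plan's value, and nothing in the article supports them. The other is that fixed adjustment would buy a calculable gain in effective sample size of 1/(1 - R^2). That is a linear-model result which does not carry over to the odds ratio from a mixed logistic model, and the article gives no R^2. No such gain is claimed here.

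**Conclusion.** The point holds in limited form. The plan names cluster-naive tests and a multi-level method for the same outcomes without saying which governs, and it lets observed baseline differences select the covariates.

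The cost of the first defect is conditional and small: about 0.7 to 1.1 percentage points of excess type I error (5.7-6.1 % instead of 5 %), assuming the plan's ICC, equal session sizes, and inference from the simple tests. It disappears, apart from the usual approximation with 22 + 22 = 44 sessions in a pairwise comparison, if the multi-level model is used. The second defect has no figure attached; its cost is that the primary model is not fixed before the data are seen. Together they leave room for the same outcome to be reported in more than one way, which is worth closing because closing it is nearly free.

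**What to change.** In the Data analysis section:
1. State that multi-level logistic regression with a random intercept for session is the analysis for the quit rates at 3 and 6 months and for the other binary outcomes.
2. Limit the chi-square, Mann-Whitney and t-tests to description, and say that no conclusion rests on them.
3. Replace the conditional adjustment clause with a short covariate set fixed before outcomes are examined by arm, drawn from variables already collected: for example cigarettes per day, time to first cigarette, past quit attempts, readiness to quit, age and sex.
4. Report crude quit rates by arm beside the adjusted odds ratio.

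The cost is wording only: no new data, visits or participants. The one small downside is that the adjusted odds ratio is conditional on the covariates, which is why the crude rates should stand next to it.
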